## Methods

### Overview

We developed the video game (*Night Shift*) in collaboration with Schell Games (Pittsburgh, PA) through an iterative process involving behavioral scientists, cognitive psychologists, trauma surgeons, and emergency medicine physicians. We plan to compare the impact of *Night Shift* with that of a standard educational program on simulated triage decisions made by a convenience sample of emergency medicine physicians. We will recruit physicians working at non-trauma centers, randomize them to play *Night Shift* or to review a standard educational program, and assess their decision making on a validated virtual simulation.

The virtual simulation allows us to assess physician performance in terms of the number of severely injured patients not transferred to trauma centers (under-triage). We can also assess the effect of *Night Shift* on physician heuristics, by experimentally manipulating cognitive load in the simulation. Psychological theory predicts that cognitive load will increase reliance on heuristics, thereby increasing the under-triage rate in situations where those heuristics are inaccurate [24]. Our target heuristic is representativeness. In the context of trauma triage, it would entail forming an initial impression based on how typical a patient appears of the severely injured.

We hypothesize that: a) physicians exposed to *Night Shift* will have lower rates of under-triage compared to those exposed to the educational program, and b) cognitive load will not degrade triage performance among physicians exposed to *Night Shift* as much as it will among those exposed to the educational program.

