#### Randomization and blinding

We will randomize eligible physicians to complete (a) either *Night Shift* or the educational intervention, *myATLS and Trauma Life Support MCQ Review,* and (b) either the control or cognitive load version of a virtual simulation [Fig. 1]. We will generate a randomization scheme using Stata 13.0 (Statacorp, College Station, TX, USA) statistical software, using random block sizes of 4 or 8. After registering the participant, study personnel will obtain the intervention assignment from a central database. Although we cannot blind study personnel and participants to the intervention after allocation, we will mask group assignment during the analysis phase.

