There are two versions of the simulation: a control and a cognitive load condition. As mentioned earlier, cognitive load is expected to increase reliance on heuristics [24]. When poorly calibrated, these heuristics result in predictable errors. By varying cognitive load, we can assess the effect of the interventions on physicians’ heuristics (a secondary outcome measure). Specifically, a comparison of the difference in performance under control and cognitive load conditions of physicians in the two arms of the study will provide insight into the mechanism by which the interventions work. If physicians exposed to *Night Shift* demonstrate both lower under-triage rates, and less effect of cognitive load on performance, we can infer that *Night Shift* functions by recalibrating heuristics. In contrast, if physicians exposed to *Night Shift* perform better in general but have the same rate of errors when working under cognitive load as physicians exposed to the educational module, then we can infer that *Night Shift* functions through some alternative mechanism.

We operationalize cognitive load in two ways. First, we vary the complexity of the non-trauma cases. In the control arm, non-trauma cases have routine complaints (e.g. appendicitis), arrive hemodynamically stable, and do not deteriorate over the course of the simulation. In the cognitive load arm, non-trauma cases are critically ill (e.g. have sepsis), arrive hemodynamically unstable, and deteriorate without adequate management. Second, we reduce the number of rooms that physicians can use to evaluate patients, from eight in the control arm to four in the cognitive load arm, which increases the number of distractors that they receive.

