### Human subjects and power calculation

We have designed the experiment to capture a moderate effect (one-half a standard deviation) of the interventions on the difference between the under-triage rates of physicians who complete the game and educational program with an alpha of 0.05 and a power of 80 % [29]. Based on prior studies, we anticipate a 70 % response rate and will recruit 366 physicians [15, 16].

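### The second branch of the mechanism rule leaves the contrast the plan tests, and read loosely it infers an alternative mechanism from a null result the design cannot establish

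*Protocol article*

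**What the plan says.** Each physician is randomized to the game or the educational program and also to "either the control or cognitive load version of a virtual simulation" (Randomization and blinding), which gives four cells.

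Hypothesis b (Overview, repeated under Physician performance) is that "cognitive load will not degrade triage performance among physicians exposed to" the game as much as among those given the educational program. Physician performance plans an ANOVA with intervention, load and their interaction.

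Outcome assessment announces the control-versus-load difference in performance, compared between arms, as the route to the mechanism. It then gives a two-branch rule:

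- **Branch 1.** If game physicians "demonstrate both lower under-triage rates, and less effect of cognitive load on performance", the game works by recalibrating heuristics.
- **Branch 2.** If they "perform better in general but have the same rate of errors when working under cognitive load as physicians exposed to the educational module", it works in some other way.

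Human subjects and power calculation sizes the trial for a "moderate effect (one-half a standard deviation") in "the difference between the under-triage rates of physicians who complete the game and educational program", "with an alpha of 0.05 and a power of 80"%. It adds: "we anticipate a 70 % response rate and will recruit 366 physicians". No interaction size and no equivalence margin are given.

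**The concern.** The announced comparison, branch 1, hypothesis b and the ANOVA interaction all use one quantity: the load effect in one arm minus the load effect in the other. Branch 2 uses a different one, the between-arm difference in the loaded cells only. The two branches are presented as alternatives but do not divide the possible results between them.

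If branch 2 is taken as a loose way of saying that load has the same effect in both arms, another difficulty appears. The rule then permits a positive statement about mechanism from a finding of sameness, while the planned test can only fail to find a difference.

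At stake is what the secondary outcome may be used to claim. The article presents this comparison as its evidence on mechanism.

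**Working it through.** **Inputs.** Two-sided alpha 0.05 (sidedness is not stated, but two-sided reproduces the sample size), power 80%, effect 0.5 SD, 366 recruited and 70% response, all from the power section. Four cells come from Randomization and blinding; equal cells are assumed.

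**1. The plan's own figure.** Normal approximation: n per group = 2(1.960 + 0.842)²/0.5² = 62.8, so 63; the t-test gives 63.8, so 64. Four cells: 4 × 64 = 256, and 256/0.70 = 365.7, so 366. The figure reproduces. Two groups alone would give 128/0.70 = 182.9, so 183. The design therefore has about 64 evaluable physicians per cell and 128 per arm.

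**2. Branch 2 read literally.** Let the load effect be under-triage under load minus under-triage in the control condition, and let D be the game arm's load effect minus the education arm's. Attenuation (hypothesis b) is D < 0. If the game's benefit is b_C in control and b_L under load, its overall benefit is (b_C + b_L)/2 and D = b_C − b_L. Setting b_L = 0 with a positive overall benefit forces b_C > 0, so D > 0: load degrades the game arm more. The rates below are assumed for illustration.

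| Pattern | Education, control/load | Game, control/load | Load effects (education, game) | D | Branch met |
|---|---|---|---|---|---|
| Equal under load | 60/70% | 40/70% | +10, +30 | +20 points | 2 |
| Parallel benefit | 60/70% | 45/55% | +10, +10 | 0 | neither |

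The parallel pattern is the natural complement of branch 1, and the rule as written does not cover it.

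**3. Branch 2 read as the same load effect.** SE(D) = SD × √(4/64) = 0.25 SD. The 95% CI half-width is 1.96 × 0.25 = 0.49 SD.

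Power ≈ Φ(|D|/0.25 − 1.96):

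- |D| = 0.25 SD: Φ(−0.96) = 0.17
- |D| = 0.5 SD: Φ(0.04) = 0.52 (0.513 by noncentral t)
- 80% power needs |D| = (1.960 + 0.842) × 0.25 = 0.70 SD

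**4. How well the pattern separates mechanisms.** Assume a main effect of 0.5 SD. Its SE is √(2/128) = 0.125 SD, so the probability of significance is Φ(4 − 1.96) = 0.979. In a balanced design the main effect and interaction contrasts are orthogonal, so the probabilities multiply:

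| True attenuation (assumed) | P(interaction not significant) | P(main effect significant and interaction not) |
|---|---|---|
| 0 | 0.950 | 0.979 × 0.950 = 0.93 |
| 0.25 SD | 0.830 | 0.979 × 0.830 = 0.81 |
| 0.5 SD | 0.484 | 0.979 × 0.484 = 0.47 |

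The pattern is only 0.93/0.81 = 1.1 times as likely with no interaction as with 0.25 SD, and 0.93/0.47 = 2.0 times as likely as with 0.5 SD.

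**5. What a claim of sameness would need.** Two one-sided tests at 5%, true D = 0, margin m (assumed): power = 2Φ(m/0.25 − 1.645) − 1, set to 0 if negative; n per cell for 80% power = 4(1.645 + 1.282)²/m².

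| Margin | Power at 64 per cell | n per cell for 80% |
|---|---|---|
| 0.25 SD | 0% | 549 |
| 0.5 SD | 28% | 138 |
| 0.75 SD | 82% | 61 |

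**The case against.** The best defence is that the right contrast is already there. The same paragraph announces it, branch 1 uses it, and the ANOVA tests it. Branch 2 is introduced as the opposite of branch 1, so a sympathetic reader would take it to mean the same degradation under load. That reading is plausible and also covers the parallel pattern. It reduces the contrast problem to wording, but it leads directly to the null-result problem in steps 3 to 5.

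It can also be said that the article states no significance criterion, and that judging a non-significant interaction belongs in an analysis plan. That is fair as far as it goes. However, the article does state that the inference may be drawn from sameness, and that is too strong for a comparison this imprecise.

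Four stronger readings are tempting, and the document does not support them:

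- **That the whole rule, or the ANOVA, uses the wrong contrast.** Only branch 2 departs from it.
- **That a literal branch 2 result leads to a wrong conclusion.** On the article's theory, load increases reliance on heuristics. A game advantage that vanishes under load does argue against recalibration. The literal branch is incomplete and misaligned, but its inference is not perverse.
- **That the rule misnames the mechanism about half the time.** The chance of a non-significant interaction alone is about 48% to 49% at 0.5 SD, but branch 2 also requires better overall performance. The joint figure is 47%, and it rests on assumed effect sizes.
- **That omitting a check that load worked is an error.** Branch 1 presupposes a load effect in the comparator, and load is a factor in the ANOVA. An explicit condition is a useful addition.

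**Conclusion.** The point holds for branch 2 only. Literally, it describes a benefit confined to the control condition and omits the equal-benefit pattern. Loosely, it infers an alternative mechanism from a null with no margin, when the 95% CI half-width is about 0.49 SD and power is 17% to 51% for interactions of 0.25 to 0.5 SD. An observed pattern of better overall with no significant interaction would be common whether or not recalibration is real (93% with no interaction, 81% at 0.25 SD, 47% at 0.5 SD), so it separates the mechanisms poorly.

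These figures assume equal cells and that 70% of the 366 provide outcome data. The Analyses section defines response as starting the intervention and excludes those who do not finish the simulation, so cells would be smaller if fewer finish. The interaction sizes, the 0.5 SD main effect in step 4 and the equivalence margins are assumptions; the document gives 0.5 SD only for the game-versus-education difference.

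Severity is moderate. A secondary interpretation is affected. Nothing here faults the sample size of 366, which reproduces for its stated purpose, or the primary comparison.

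**What to change.** Rewrite the mechanism paragraph so that every branch rests on the difference of load effects between arms (D), reported with its 95% CI:

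1. **Consistent with recalibration**, only if the game arm has lower under-triage, load raises under-triage in the education arm, and the CI for D lies wholly on the attenuation side.
2. **Load degrades the game arm more**, if the CI lies wholly on the other side. This argues against recalibration.
3. **Mechanism not determined**, if the CI covers zero, unless an equivalence margin was fixed before results are seen and is met. Step 5 shows that only a wide margin is within reach at 64 per cell.

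The cost is rewording one paragraph and giving up a claim the design cannot support. No new participants, data or model are needed. The article gives the trial status as recruiting, so the change should be made and dated before outcome data are examined.

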#### Questionnaire to assess personal characteristics

Each physician will complete a questionnaire querying age, sex, race, ethnicity, educational background (board certification, ATLS certification, years since completion of residency). We will also assess individual differences that might vary between the two samples, and might influence the efficacy of the different interventions. Physicians will complete the Big Five Inventory-10, a ten-item instrument that measures personality traits [27].

#### Questionnaire to assess usability and tolerability of interventions

To measure the tolerability of the interventions, we will ask physicians to provide qualitative feedback about the experience. Additionally, we will ask physicians who use Night Shift to complete the Narrative Engagement Scale developed and validated by Busselle and Bilandzic [28]. The instrument has 12 items that measure narrative understanding, attentional focus, narrative presence, and emotional engagement. It will allow us to explore causes for *Night Shift*’s success or failure at changing physician decision making, in future analyses.

### Analyses

We will calculate the response rate as the proportion of enrolled physicians who start to use their assigned intervention, and the completion rate as the proportion who finish the virtual simulation. We will include physicians in the analysis who do not spend one hour on their assigned intervention (i.e. evaluating it in terms of intention-to-treat). We will exclude physicians who do not complete the virtual simulation (i.e., those for whom we have missing outcome data).

We will summarize physician characteristics (including personality traits) using means (standard deviations) for continuous variables and proportions (%) for categorical variables, and will compare the distribution of characteristics between the two intervention groups using Students *t*-test and chi-squares as appropriate.

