### Study protocol

Upon enrollment, subject physicians receive an iPad mini 2 with their intervention pre-loaded, along with written instructions on how to complete the study protocol. They will receive weekly reminder emails to complete the protocol for the duration of the study. We will ask participants to spend a minimum of one hour completing the intervention task. After completing it, they will be instructed to log in to a website that hosts: a) the virtual simulation; b) a questionnaire about their personal information, and c) a questionnaire about the intervention’s tolerability. Completing the simulation and two questionnaires will take approximately one hour. Participants will be able to complete the two portions of the study protocol at their convenience, within 1 month of enrollment. They will keep the iPad mini 2 as an honorarium (approximate value $260).

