#### Physician performance

We hypothesize that: a) physicians exposed to *Night Shift* will have lower rates of under-triage compared to those exposed to the educational program, and b) cognitive load will not degrade triage performance among physicians exposed to *Night Shift* as much as it will among those exposed to the educational program.

To test these hypotheses, we will first score participants’ performance on each trauma case based on a review of their disposition decisions, using American College of Surgeons guidelines as the gold standard [4]. We will calculate an under-triage rate for each physician:$$ \frac{\mathrm{number}\ \mathrm{o}\mathrm{f}\ \mathrm{severely}\ \mathrm{injured}\ \mathrm{patients}\ \mathrm{not}\ \mathrm{t}\mathrm{ransferred}\ \mathrm{t}\mathrm{o}\ \mathrm{t}\mathrm{rauma}\ \mathrm{centers}}{\mathrm{total}\ \mathrm{number}\ \mathrm{o}\mathrm{f}\ \mathrm{severely}\ \mathrm{injured}\ \mathrm{patients}} $$

We will assess the influence of the intervention (game or educational program), cognitive load (absent or present), and the interaction between these factors on physicians’ under-triage rates using an ANOVA.

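### The planned ANOVA is valid but uses none of the physician characteristics already collected; a pre-specified ANCOVA would add modest precision, mainly for the interaction, and should replace the between-arm significance tests

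*Protocol article*

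**What the plan says.** All references are to the protocol article.

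- **Characteristics collected** (Questionnaire to assess personal characteristics): the section lists the items in one sentence, "Each physician will complete a questionnaire querying age, sex, race, ethnicity, educational background (board certification, ATLS certification, years since completion of residency", followed by a ten-item personality inventory. The reason given for measuring the latter is "individual differences that might vary between the two samples, and might influence the efficacy of the different interventions".
- **When they are collected** (Study protocol): the questionnaire follows the intervention. "After completing it, they will be instructed to log in to a website that hosts" the simulation and both questionnaires.
- **What is done with them** (Analyses): they are summarised, and the investigators "will compare the distribution of characteristics between the two intervention groups using Students" t-tests and chi-squares. No further use is stated.
- **Who is analysed** (Analyses): "We will exclude physicians who do not complete the virtual simulation".
- **Outcome model** (Physician performance): "We will assess the influence of the intervention (game or educational program), cognitive load (absent or present), and the interaction between these factors", by ANOVA on each physician's under-triage rate. No covariate is named.
- **Size** (Human subjects and power calculation): a "moderate effect (one-half a standard deviation"), alpha 0.05, power 80%, an anticipated 70% response, 366 physicians.

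**The concern.** The trial collects items that plausibly bear on triage skill. ATLS certification is the clearest: the section on the educational control describes ATLS as teaching physicians, among other things, to judge when a patient needs more than their hospital can provide, which is close to the decision being scored. The stated plan puts these items through significance tests and then fits a model without them.

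The tests serve neither purpose they might have. As a check on randomisation they have nothing to establish, because any imbalance at allocation is due to chance. As a check on dropout they are weak, because they compare only physicians who reached the website. The article gives no rule for what follows a significant result, which leaves room for covariates to be chosen after the data are seen.

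At stake is precision, chiefly for the intervention-by-load interaction. That contrast carries hypothesis (b) and, under Outcome assessment, the inference about whether the game recalibrates heuristics.

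**Working it through.** **1. Reproduce the stated sample size.** Inputs: 0.5 SD, alpha 0.05 (two-sided assumed; the article does not say), power 80%, 70% response. A two-sample t-test needs 63.8, so 64 per group. Four cells give 4 × 64 = 256, and 256 / 0.70 = 365.7, so 366. The stated figure is matched exactly. (Two groups only would give 128 / 0.70 = 183.) The checks below therefore use 64 completers per cell and 128 per arm. This treats the 70% as completion of the simulation, although the Analyses section defines response as starting the intervention.

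**2. Power of the stated, unadjusted model**, in SD units, normal approximation, equal cells.

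- Main effect: SE = √(2/128) = 0.125. Power = Φ(0.5/0.125 − 1.96) = Φ(2.04) = 97.9%. Effect detectable at 80% power: 2.80 × 0.125 = 0.35 SD.
- Interaction (difference of differences): SE = √(4/64) = 0.25. Power = Φ(0.5/0.25 − 1.96) = Φ(0.04) = 51.6%. A t reference gives 51.3%.

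**3. Power with covariates.** If they explain a share R² of the within-cell variance, each SE is multiplied by √(1 − R²). R² is an assumption; the article gives no value.

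| Assumed R² | SE ratio | Equivalent N, 256/(1 − R²) | Main effect 0.5 SD | Interaction 0.5 SD |
|---|---|---|---|---|
| 0 | 1.000 | 256 | 97.9% | 51.6% |
| 5% | 0.975 | 269 | 98.4% | 53.7% |
| 10% | 0.949 | 284 | 98.8% | 55.9% |
| 20% | 0.894 | 320 | 99.4% | 60.9% |

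A t reference gives 53.4%, 55.6% and 60.6% for the interaction.

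**4. What the planned tests can show.**

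- Count: age, sex, race, ethnicity, board certification, ATLS certification and years since residency make 7. Five personality traits, if scored separately, make 12. If independent and each tested at 0.05, the chance of at least one significant difference under sound randomisation is 1 − 0.95¹² = 46%.
- Sensitivity: with 128 per arm, a continuous characteristic must differ by about 0.35 SD before the test has 80% power to detect it. A non-significant result is little evidence that loss was unselective.

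**5. How far chance imbalance could move the estimate.** An imbalance at the 1.96-SE limit is 1.96 × 0.125 = 0.245 SD of the covariate. The shift in the outcome is √R² × 0.245: 0.055 SD at R² = 5%, 0.077 at 10%, 0.110 at 20%. The unadjusted standard error already allows for this variation.

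**The case against.** The strongest reply is that nothing in the stated model is wrong. Physicians are randomised to intervention and to simulation version, and the ANOVA analyses exactly those two factors and their interaction. Its standard error already covers chance imbalance. **This stands.** A reader might infer that the unadjusted ANOVA is biased, or leaves chance imbalance uncorrected in a damaging sense. The article does not support that reading.

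A reader might also infer that adjustment would repair the dropout problem. It would not in general. That problem comes from excluding non-completers. Covariates help only so far as these three items explain who drops out, and the article gives no evidence on that. Most non-completers would also have no questionnaire data. **This stands.**

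The gain may be small. No prognostic strength is given, and the protocol's own rationale speaks of influence on efficacy, which is effect modification. Each score rests on only three severely injured cases. If the between-case correlation were 0.1 or 0.2 (assumed), the share of score variance lying between physicians would be 3 × 0.1/1.2 = 25% or 3 × 0.2/1.4 = 43%. Reaching R² = 20% would then require the covariates to explain 0.20/0.25 = 80% or 0.20/0.43 = 47% of all true differences between physicians. **This stands in part:** the lower end of the range is easier to believe, and even the upper end leaves interaction power well below 80%.

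Finally, an unseen analysis plan may add adjusted analyses, and the article never says that the tests will steer the model. Both are fair. But the model and the tests are stated here, so the point concerns a better choice than the one stated and does not rest on missing detail.

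**Conclusion.** The point holds as a modest efficiency improvement together with the removal of uninformative tests. At an assumed R² of 5% to 20%, interaction power at 0.5 SD goes from about 51-52% to 53-61%. The primary comparison at the planned 0.5 SD gains at most about 1.5 percentage points (97.9% to 99.4%), because 128 completers per arm already give it ample power. These figures rest on equal cells, 256 completers, two-sided alpha 0.05, and an R² that the article does not supply. Adjustment does not solve the low interaction power, and it corrects imbalance from dropout only to the extent that the three factors explain dropout.

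**What to change.** Change the analysis wording as follows.

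- **Primary model:** an ANCOVA with intervention, cognitive load, their interaction, ATLS certification, board certification and years since residency, named before the data are examined. Define all three as status at enrolment, since the questionnaire is completed afterwards.
- **Supporting analysis:** the unadjusted ANOVA as now stated.
- **Missing items:** keep every simulation completer in the model, filling a missing questionnaire item by simple covariate imputation that does not use the arm.
- **Personality scores:** do not adjust for them, because they are self-reported after the intervention and could be affected by it.
- **Characteristics table:** show them descriptively for each of the four cells, without p-values.

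The items are already collected, so the cost is wording, possibly including the enrolment reference date in the questionnaire. The statistical cost is small: with one parameter per covariate, residual degrees of freedom fall from 256 − 4 = 252 to 249. Describing non-completers on these factors would require collecting them at enrolment, which is a separate and larger change.
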